#### Secondary Study Parameters and End Points

The secondary study parameters (Table 2) and end points are as follows: (1) objective pain metric (volume of administered pain medication); (2) respiratory rate and tidal volume; (3) HR; (4) blood pressure; (5) neuroinflammation blood markers (IL6, NGAL, CRP, and serum TPSO); (6) behavioral indicators of neuroinflammation (delirium [31] and POCD incidence); and (7) EEG markers of neuroinflammation (alpha power, delta/alpha power ratio, and entropy).

**Table 2 table2:** Secondary study parameters.

Outcome	Metric	Statistics
Objective pain measure	Pain medication dosage (ccs)	Chi-square test
Neuroinflammation, blood markers	IL6^a^, NGAL^b^, CRP^c^, and serum TPSO^d^	*F* test (RM^e^ ANOVA, pre-post)
Neuroinflammation, behavioral indication	Incidence delirium and incidence POCD^f^	*F* test (one-way ANOVA)
Neuroinflammation, EEG^g^ indication	Alpha power, alpha/delta power, and entropy	*F* test (RM ANOVA same as primary)
Neuroinflammation, physiological	HR^h^, respiration rate, and blood pressure	*F* test (RM ANOVA same as primary)

^a^IL6: interleukin-6.

^b^NGAL: neutrophil gelatinase–associated lipocalin.

^c^CRP: C-reactive protein.

^d^TPSO: translocator protein.

^e^RM: repeated measures.

^f^POCD: postoperative cognitive decline.

^g^EEG: electroencephalogram.

^h^HR: heart rate.

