#### Pulmonary Ventilation

Respiration rate and tidal volume have been linked to subjective pain experience in the literature [4]. Therefore, in order to see whether our pain findings extend from subjective to objective physiological measures, we will explore the association between these 2 objective metrics and subjective pain VAS ratings. A wearable biosensor that measures pulmonary ventilation metrics [35] will be placed on the chest of patients with an adhesive sticker and removed at the end of the day.

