### Primary Study Parameters

Pain ratings will be collected 4 times a day with a VAS. VAS mean and SD will be reported, and box plots, histograms as well as *P* values for Kolmogorov-Smirnov tests will be evaluated for normality of distribution. A univariate, one-way repeated measures (RM) ANOVA will be conducted with factors group (live music intervention, recorded music active control, and standard care control) by time points (1, 2, 3, 4). The α significance threshold will be .05. The result of interest is the significance of the training×time point interaction, that is, whether the course of the data across time points was altered by the training type. Data are planned with 4 time points; in case of up to 2 missing time points, data will be interpolated [37]. Cases with more than 2 missing time points will be excluded from the analysis. Alternatively, if the residuals of the ANOVA are not normally distributed, a similar Kruskal-Wallis one-way ANOVA will be conducted.

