### Secondary Study Parameters

For metrics that are collected on the same schedule as the VAS (EEG alpha power, delta/alpha power ratio, entropy metrics, HR, respiration rate, and blood pressure), the values per participant will be entered into the same *F* test described for the VAS ratings (as well as correlated with other baseline parameters as described in the “Other Parameters” section). For blood marker metrics that have 2 data collection points, a similar RM ANOVA will be conducted, but with 2 as opposed to 4 measures, and a significant interaction between treatment and time point would indicate whether treatment significantly impacted the amount of the neuroinflammatory blood marker. Categorical incidence metrics (delirium and POCD) will be evaluated with a one-way ANOVA to determine whether treatment impacted these neuroinflammatory-related complications. Delirium and signs of delirium will be perceived using the DOSS. The DOSS is a screening instrument for delirium, consisting of 13 items, and will be filled by a registered nurse during hospital admission until discharge. Nurses have frequent contact with the patients and are in a good position to observe behavior changes 24 hours a day when patients are admitted. The DOSS is already part of a routine in the surgical wards and all registered nurses are already trained. Likewise, scalar pain medication dosage will be averaged over 24-hour periods per patient and entered into a chi-square test to determine whether the dosage was significantly different across the 3 treatment groups. As this is exploratory and serves to inform future hypothesis-directed testing, we will not correct for multiple comparisons.

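### Pain medication dosage is a continuous per-patient average, but the plan assigns it a chi-square test, which does not answer whether dosage differs between the three groups

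*Protocol article*

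**What the plan says.** Dosage is the first secondary end point in the section Secondary Study Parameters and End Points. Table 2 there labels its row as the objective pain measure, gives the metric in ccs and names a chi-square test.

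The Statistical Analysis part (Secondary Study Parameters) says the same in prose: "scalar pain medication dosage will be averaged over 24-hour periods per patient and entered into a chi-square test", the purpose being "to determine whether the dosage was significantly different across the 3 treatment groups". No grouping of doses into categories is described in either place.

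The same paragraph says: "Categorical incidence metrics (delirium and POCD) will be evaluated with a one-way ANOVA". It closes the secondary analyses with: "As this is exploratory and serves to inform future hypothesis-directed testing, we will not correct for multiple comparisons".

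**The concern.** The authors themselves call the variable scalar. Its value is an average quantity per patient, while a Pearson chi-square test needs counts of patients in categories. The outcomes in the same paragraph that really are categories, delirium and POCD, receive an ANOVA. The two tests look transposed.

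The Introduction wants to extend the pain finding from subjective to more objective measures and names medication dosage first among its examples. The secondary results are also meant to shape later hypotheses. A P value for dosage that carries no information about dose, or whose error rate depends on the unit of measurement, would mislead that later work.

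**Working it through.** **Inputs from the article.** Three groups (G=3), 120 per group, N=360 after padding, 327 before (Power section). The article gives no mean, spread, effect size or power for dosage. I read the text as one averaged value per patient.

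**The plan's own figure.** The sample size concerns only the primary interaction, and it reproduces. f = √(0.051/0.949) = 0.23182. λ = f² × 327 = 17.573. The df are (3−1)(4−1) = 6 and (327−3)×3 = 972. The critical F is 2.1079 and power 0.9008, as in Table 3. Nothing below touches it.

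**Reading 1: per-patient averages entered as written, all distinct.** The table is group by dose value, with one patient in each column.
- Pearson's statistic is χ² = N[Σ O²/(row total × column total) − 1].
- Each column total is 1, so each patient contributes 1/n_g. Summed within a group this is 1, and over the groups it is G.
- Hence χ² = N(G−1) and df = (N−1)(G−1).
- N=360: χ² = 360×2 = 720, df = 359×2 = 718, P = .472.
- N=327: χ² = 654, df = 652, P = .471.

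The doses do not appear in the formula. In simulation at N=360, P stayed at .472 under no effect and with the live arm shifted by 0.5 SD and by 1 SD. Power is zero.

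**Reading 2: doses tied or binned.** The test is then a genuine test of category distributions. Assumed for illustration: log-normal dose, log-SD 0.6, median about 4.5 cc, 120 per group, shifts of 0.5 SD (live) and 0.25 SD (recorded) on the log scale against standard care; 1,000 runs for whole-cc categories, 2,000 for the others.

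| Analysis | Type I error | Power |
|---|---|---|
| Chi-square, whole-cc categories | 0.028 | 0.37 |
| Chi-square, median split | 0.052 | 0.80 |
| One-way ANOVA on log dose | 0.053 | 0.93 |
| Kruskal-Wallis | 0.046 | 0.93 |

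**Reading 3: group totals tested against equality.** With no true difference, the statistic behaves roughly as V × χ² on 2 df, where V = patient variance ÷ patient mean in the chosen unit. The rejection rate is therefore about exp(−5.991/(2V)) = 0.05^(1/V).
- V=0.5: 0.05² = 0.25%
- V=1: 5%
- V=2: 22%
- V=10: 74%

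Multiplying the unit by a constant multiplies V by it. For the log-normal example, simulated rejection under no difference was 25.7% in cc, 88.2% with totals multiplied by 10, and 0% with totals divided by 10. A test on the three group means fails the other way: it never rejected, even with the live arm shifted by 1 SD.

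**The companion mismatch.** For a 0/1 outcome, χ² = N × SSB/SST (between-group over total sum of squares), and F is a monotone function of the same ratio. At the chi-square threshold of 5.991 with N=360, SSB/SST = 0.01664, so F = (0.01664/2) ÷ (0.98336/357) = 3.021. The critical F on 2 and 357 df is also 3.021. In simulation the ANOVA's type I error was 3.9–5.1% at incidence rates of 1–20%. That swap therefore matters little for the P value.

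**The case against.** The best defence has four parts.

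1. **Chi-square may be shorthand for Kruskal-Wallis**, whose statistic is referred to a chi-square distribution. The article does not support this. Under Primary Study Parameters it names that test outright ("a similar Kruskal-Wallis one-way ANOVA will be conducted"), and only as a fallback for the pain ratings.

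2. **The fixed P value needs distinct doses.** This stands. Dose data can contain many zeros or repeated values, and the result of 720 on 718 df then no longer holds. A reader might infer that the planned test is void in every case, but with ties or bins it is inefficient rather than void. The article states neither binning nor rounding, so the literal reading is fair, but it is conditional.

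3. **Dosage is not the sole route to an objective measure.** This also stands. The row label in Table 2 might suggest it is, but the Introduction pairs dosage with respiration rate, and the Pulmonary Ventilation section says of respiration rate and tidal volume: "we will explore the association between these 2 objective metrics and subjective pain VAS ratings". Respiration rate has its own repeated measures ANOVA.

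4. **The outcome is exploratory.** True, and it limits the severity. It justifies leaving multiplicity uncorrected. It does not justify a test that does not fit the variable.

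A reader might also infer that analgesic use would differ almost automatically between arms. That follows only if totals are tested and V is large, and the article does not say that totals would be entered.

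**Conclusion.** The point holds in a limited form. The article states, in two places, a test that does not match the outcome; this is not detail left to an analysis plan.

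The size depends on how the test is carried out:
- Zero power, with P fixed at .47, if the values are distinct and entered as written at N=360.
- A loss of power from 0.93 to 0.80 or 0.37 if the doses are split at the median or put in whole-cc categories. This rests on the assumed log-normal example.
- A false-positive rate anywhere from about 0% to nearly 100% if totals are used.

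The article does not say which would be done. The primary pain analysis, its alpha and the 327 patients are unaffected. This should be fixed, but it does not threaten the trial's main conclusion. The mirror-image choice for delirium and POCD is minor, and its main value here is as a sign that the two tests were transposed.

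**What to change.** In the Statistical Analysis text (Secondary Study Parameters) and in the dosage row of Table 2, replace the chi-square test with a between-group comparison of dose per patient. Use a linear model or one-way ANOVA, on a transformed scale if dose is skewed, or Kruskal-Wallis if it is skewed with many zeros. Report group differences with 95% CIs.

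With one-way ANOVA at N=360, power would be 0.38, 0.72, 0.93 and 0.99 at f = 0.10, 0.15, 0.20 and 0.25. These effect sizes are assumptions, since the article gives none for dosage.

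As a companion correction, use chi-square or Fisher's exact test for delirium and POCD incidence in the same paragraph and table. This changes the P value little except when events are few.

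The cost is a few words of text and two table cells. No data, patients or procedures change. Data collection is expected to run until 2026 (Results), so the wording can be corrected before the analysis.

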### Other Study Parameters

Posthoc analyses will be conducted to inform recommendations for participant grouping in future studies. Continuous baseline parameters (eg, age; see “Other Parameters” section for a full list) will be treated as covariates in an ANOVA in order to see whether the addition of these elements improves the model for each outcome. Similarly, categorical baseline parameters (eg, type of surgery) will be coded and entered as an additional factor (two-way RM ANOVA: treatment×baseline×time point) to see whether the additional factor can explain more variance than in the primary analysis model.

#### Power

The sample size was calculated using G*Power 3.1 [38], an industry-standard software. Below, we explain the parameters for an RM between-subjects univariate ANOVA as well as the final sample size. The calculation was based on the desired ability to detect a within-between interaction (intervention group×time point), with recommended internal settings from [39], which would effectively indicate whether the live music intervention altered the slope of outcome measurements compared to the recorded music or do-nothing control groups.

The effect size (partial η^2^=0.051, converted to f=0.2318206) was determined from a retrospective RM ANOVA with published data [1].

Alpha: As we have a single quantitative outcome measure, alpha may remain at the conventional .05 significance threshold.Power: Following recent recommendations to set power above the typical 0.8 to 0.9 and higher [40], the threshold was set at 0.9.Number of groups or measurements: The design calls for 3 groups, with 4 RM (see “Study Design” section; before treatment, after treatment, 3-hour, and 6-hour follow-up) for each participant.Nonsphericity correction: As mentioned earlier, retrospective analyses were conducted with the data published in [1]. The ANOVA conducted with that data passed the assumption of sphericity (*P*=.07); therefore, no correction (1) was entered in the G*Power calculation.Sample size: The sample size (n=327, Table 3) outputted from G*Power represents the total number of participants in a 3-group design required to achieve 0.9 power with an effect size of ~0.232-109 per group. Padding for a 10% dropout rate raises the per group n to 120, for a total N of 360.

**Table 3 table3:** G*Power sample size calculation.

Parameters			Value

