**Input parameters**			
	Effect size *f*(*V*)	0.2318206	
	α err prob	.05	
	Power (1−β err prob)	0.9	
	Number of groups	3	
	Number of measurements	4	
	Nonsphericity correction ε	1	

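### The sample size takes epsilon = 1 from a non-significant sphericity test (P=.07), so the stated 0.90 power is the maximum with respect to epsilon and no range is given

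*Protocol article*

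**What the plan says.** **Primary test.** Under Primary Study Parameters, the protocol article states: "A univariate, one-way repeated measures (RM) ANOVA will be conducted with factors group" (three groups) by four time points. It continues: "The result of interest is the significance of the training×time point interaction". On the level it says: "The α significance threshold will be .05". The section describes normality checks, a rank-based fallback and interpolation of missing ratings. It does not mention sphericity.

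**Sample size.** Under Power, the effect size is a partial eta-squared of 0.051, "converted to f=0.2318206", and it "was determined from a retrospective RM ANOVA with published data". On power, "the threshold was set at 0.9". The ANOVA on those earlier data is said to have met the sphericity assumption, with P=.07, and "therefore, no correction (1) was entered in the G*Power calculation". Table 3 accordingly lists "Nonsphericity correction ε" as 1 and reports N=327, noncentrality 17.5732385, critical F 2.1078920 on 6 and 972 df, and power 0.9007901.

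**Timing.** Study Design and Table 1 place the four ratings before the session, directly after it, and 3 and 6 hours later. In Table 1 these fall at about 10:30, 11:00, 14:00 and 17:00.

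**The concern.** The step from P=.07 to epsilon = 1 is not a valid inference. A sphericity test that just misses significance says that the data did not exclude sphericity. It does not estimate epsilon, and it does not justify the most favourable value. With four repeated measures epsilon lies between 1/3 and 1.

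The schedule gives a reason to expect some departure. The gaps between ratings are about 0.5, 3 and 3 hours. If ratings close in time correlate more strongly than ratings further apart, the variances of the differences are unequal and sphericity fails. Unequal spacing alone does not cause this, since a constant correlation would satisfy sphericity, but it makes a departure plausible.

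Two things are affected. The first is the power figure on which the sample size rests. The second is the error rate of the univariate interaction test, which carries the primary conclusion and is liberal if run uncorrected when epsilon is below 1.

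**Working it through.** **Inputs from the protocol.** Groups k=3, measurements m=4, N=327, alpha=0.05, partial eta-squared=0.051 (Power section and Table 3).

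**Assumed input.** Epsilon below 1. The documents give no value, so a range is shown.

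**1. Reproduce Table 3 at epsilon = 1.**
- f² = 0.051/0.949 = 0.053741, so f = 0.23182, as stated.
- Noncentrality = f² × N = 0.053741 × 327 = 17.573, as stated.
- df1 = (k−1)(m−1) = 6 and df2 = (N−k)(m−1) = 324 × 3 = 972, as stated.
- Critical F = 2.1079 and power from the noncentral F = 0.9008. The smallest N that reaches 0.90 is 327. All agree with Table 3.

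**2. Vary epsilon and hold everything else fixed.** For the epsilon-corrected test, df1 = 6ε, df2 = 972ε and noncentrality = f²Nε. If the test is run uncorrected, its type I error is approximately P(F with 6ε and 972ε df > 2.1079), which is Box's approximation.

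| ε (assumed) | df1, df2 | Noncentrality | Critical F | Power at N=327 | Type I error, uncorrected F |
|---|---|---|---|---|---|
| 1 | 6, 972 | 17.57 | 2.108 | 0.901 | 0.050 |
| 0.9 | 5.4, 874.8 | 15.82 | 2.174 | 0.875 | 0.057 |
| 0.8 | 4.8, 777.6 | 14.06 | 2.253 | 0.843 | 0.065 |
| 0.7 | 4.2, 680.4 | 12.30 | 2.349 | 0.803 | 0.075 |

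Power falls steadily as ε falls. The loss is 0.901 − 0.875 = 0.026 at ε=0.9 and 0.901 − 0.803 = 0.098 at ε=0.7.

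**3. Check the type I error by simulation.** With 109 patients per group, 10,000 runs per setting and correlations that decay with time (ε from 0.86 down to 0.60), the uncorrected interaction F rejected in 0.057 to 0.079 of null trials. With the Greenhouse-Geisser correction the figure was 0.045 to 0.051. These correlation structures are illustrative and do not come from the documents.

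**4. Check whether another input could outweigh epsilon.** Table 3 takes noncentrality as f² × N. If 0.051 is an ordinary univariate partial eta-squared, that is SS effect/(SS effect + SS error), the noncentrality at N=327 would be about f² × error df = 0.053741 × 972 = 52.2. Power is then above 0.999 at ε=1 and still 0.969 at the lower bound of 1/3. The documents do not say how 0.051 was computed, so this remains open.

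**The case against.** **Silence on a correction.** A reader might infer that the trial will run its primary test without a sphericity correction. The document does not support that. Primary Study Parameters names no correction, but it does not rule one out, and a condensed article may leave this to an analysis plan that is not shown. The Power section also shows that the authors looked at sphericity. This part of the objection stands: the missing sentence is not a finding in itself. The finding is the reasoning printed under Power.

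**A heavily inflated error rate.** A reader might also infer a large type I error. Pure decay of correlation at 0.8 to 0.95 per hour on this schedule (0, 0.5, 3.5 and 6.5 hours) gives ε of 0.65 down to 0.57. That structure contains no independent rating error. If rating error is half of the total variance, ε rises to about 0.94 to 0.98, and simulated error was then 0.044 to 0.054. P=.07 itself also limits the departure. With four time points, Mauchly's test at P=.07 implies a sample ε of at least about 0.79 with 30 error df, 0.89 with 60 and 0.93 with 100. The size of the earlier study and its number of time points are not stated, so these are assumptions, but they make very low values of ε unlikely unless that study was tiny.

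**An underpowered trial.** A reader might take 0.90 as a best case overall. It is a maximum with respect to epsilon only. The noncentrality question in step 4 of the working could more than offset any loss from epsilon. Even under the protocol's own rule, power at N=327 stays above 0.80 down to ε=0.7.

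What the objection leaves intact is that the stated justification for ε=1 is invalid, that 1 is the most favourable value, and that no range is given.

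**Conclusion.** The point holds in limited form. A non-significant test at P=.07 is used as grounds for the upper bound of epsilon. Under the protocol's own f and noncentrality rule, 0.90 is therefore the maximum power with respect to epsilon, and 0.80 to 0.90 is a fair statement over ε from 0.7 to 1. If epsilon is below 1 and the interaction F is left uncorrected, it rejects somewhat too often, at about 0.057 to 0.075 for ε from 0.9 to 0.7.

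Both sizes rest on an assumed epsilon. The power figures also assume that Table 3's noncentrality rule suits the way partial eta-squared was computed. The documents do not show that sphericity fails, that the trial is underpowered, or that a correction will be withheld.

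**What to change.** - **Primary Study Parameters:** state that the primary group × time test is the Greenhouse-Geisser corrected F, or the interaction test from a mixed model with unstructured covariance, and that this does not depend on the result of a sphericity test.
- **Power and Table 3:** replace ε=1 with the epsilon estimated from the earlier data, which the retrospective ANOVA should be able to supply. Otherwise report power as a range over epsilon, for example 0.80 to 0.90 for ε from 0.7 to 1 at N=327. In the same place, say how partial eta-squared was computed, so that the noncentrality rule can be confirmed.

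The cost is a sentence or two of wording, a slightly less favourable stated power, and a negligible loss of power if sphericity does hold. Enrolment does not change.

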## Methods

### Study Design

The study will take place at the University Medical Center Groningen (UMCG), which has already hosted the Meaningful Music in Healthcare (MiMiC) live intervention [25]. The intervention study follows an on-off nonrandomized controlled trial (NCT) design [26]. The NCT is necessary for this particular intervention in practice because the live music intervention cannot easily be randomized to skip patients in the same ward without them hearing the music or seeing the musicians as they play for other patients and nurses.

In this NCT design, treatments and data collection will be conducted in 15 blocks over the course of 4 years. According to the 29-day treatment block, the three 5-day treatments (live music intervention, recorded music active control intervention, and standard care control) will be offered with a 7-day washout between treatments. The washout will minimize the number of participants whose hospital stay overlaps with another treatment. Based on the previous research (UMCG research register 201600541), we expect approximately 8 full data sets per 5-day treatment block.

Note that while the intended outcome of the music intervention is therapeutic (eg, experiencing reduced pain), the music intervention is conducted by conservatory-trained music practitioners but not by music therapists. Music therapists are licensed therapists who have a degree in music therapy including clinical training. The music practitioners in this study are primarily professional musicians who have taken 1 music-conservatory course and several internships to train them for clinical settings but they are not therapists.

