**Output** **parameters**			
	Noncentrality parameter λ	17.5732385	
	Critical *F*	2.1078920	
	Numerator df	6.0000000	
	Denominator df	972	
	Total sample size	327 (109 per group)	
	Actual power	0.9007901	

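### The stated 120 per group (360) falls one patient per group short of the required 109 (327) after the 10% dropout it is meant to cover

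*Protocol article*

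**What the plan says.** The Power section of the protocol article sizes the trial for the group by time point interaction in a repeated measures ANOVA. The inputs are a 5% test ("alpha may remain at the conventional .05 significance threshold"), target power ("the threshold was set at 0.9"), an effect size from a partial η² of 0.051 ("converted to f=0.2318206"), the layout ("The design calls for 3 groups, with 4 RM") and sphericity ("no correction (1) was entered in the G*Power calculation"). Table 3 gives the output as "327 (109 per group"), with actual power 0.9007901.

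The Power section then allows for attrition in one sentence: "Padding for a 10% dropout rate raises the per group n to 120, for a total N of 360". It does not say how the 120 was calculated.

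Separately, the Study Design section plans 15 blocks and gives a recruitment forecast: "we expect approximately 8 full data sets per 5-day treatment block".

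**The concern.** Padding for dropout is meant to leave the required number of analysable patients once the expected losses have occurred. Here the required number, the dropout rate and the padded number are all stated, and they do not agree: the padded number less 10% is below the required number. A reader would take 360 as enough to hold 0.9 power at 10% dropout, and on the protocol's own method it narrowly is not. What is at stake is the accuracy of a sample-size statement on which the trial relies, not whether the trial is viable.

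**Working it through.** **Inputs (protocol article, Power section and Table 3).** α = 0.05; target power 0.9; partial η² = 0.051; 3 groups; 4 measurements; nonsphericity correction ε = 1; required size 109 per group (327); dropout 10%; padded size 120 per group (360).

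**Step 1: reproduce the required size.**
- Effect size: f = √(0.051/0.949) = 0.2318206, as stated.
- Noncentrality: λ = f² × N = 0.2318206² × 327 = 17.5732, as in Table 3.
- Degrees of freedom: (3 − 1)(4 − 1) = 6 and (327 − 3)(4 − 1) = 972, as in Table 3.
- Critical F = 2.10789, and power from the noncentral F distribution = 0.90079, both as in Table 3.
- At N = 326 power is 0.89975, so 327 is the true minimum for 0.9 and carries no slack.

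**Step 2: apply the stated dropout to the stated size.**
- Per group: 120 × 0.9 = 108, against 109 required.
- In total: 360 × 0.9 = 324, against 327 required.
- Shortfall: 1 per group, 3 in total.

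**Step 3: power at the reduced size.** For N = 324 the same method gives λ = 17.4120, df 6 and 963, critical F = 2.10798 and power 0.8977. That is 0.0023 below the target of 0.9 and 0.0031 below the 0.9008 at N = 327.

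**Step 4: the dropout that 120 per group does cover.** 1 − 109/120 = 0.0917, or about 9.2%.

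**Step 5: size needed to cover 10% in full.**
- Equal groups: 109/0.9 = 121.1, rounded up to 122 per group, 366 in total. Check: 122 × 0.9 = 109.8, which meets 109; 121 × 0.9 = 108.9, which just misses it.
- Groups allowed to differ: 327/0.9 = 363.3, rounded up to 364.

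**Step 6: where 120 may come from.** 109 × 1.1 = 119.9 and 327 × 1.1 = 359.7, which round up to 120 and 360. This fits, but it is an inference. The schedule of 15 blocks at about 8 per treatment also multiplies to 120.

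**The case against.** **The difference is trivial.** One patient per group is lost from 109. The target is written to one decimal place, and 0.8977 rounds to 0.9. The 10% is a round planning figure given without a source, and the effect size is a retrospective estimate; uncertainty in either matters far more than a 0.003 change in power. All of this stands. It settles how much the point matters, but it does not make the three stated figures agree.

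**Not every dropout is lost to analysis.** Under Primary Study Parameters, up to two missing time points are interpolated and only cases with more than two missing are excluded. Some patients who leave early could therefore stay in the analysis. This stands too: 108 and 0.898 hold only if every dropout is excluded. It does not rescue the padding sentence, whose purpose is to allow for loss at the stated rate.

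**The method of padding is not documented.** This is correct. A reader might infer that the protocol multiplied by 1.1, but no formula is printed. The point does not need that inference: however 120 was reached, 90% of it is 108.

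**The Study Design section might seem to give 120 another meaning.** A reader could multiply 15 blocks by about 8 full data sets, obtain 120 completers per group, and conclude that the protocol uses 120 for enrolled patients in one place and completers in another, so that it is unclear when a group is full. The text does not support this. That section never states 120 and sets no rule for when a group is full; it offers an approximate forecast of yield. Taken literally, 120 complete data sets would exceed 109 and there would be no shortfall. However, only the Power section fixes the planned number, and there 120 is the figure after padding for dropout.

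**Conclusion.** The padding sentence is wrong as written, by a very small amount. At the stated 10% dropout, 120 per group leaves 108 (324 in total) against the 109 (327) that the protocol says it needs. Power is then 0.898 instead of 0.901, about 0.002 below the 0.9 target. This rests on equal groups, on the protocol's own effect size and sphericity assumption, and on every dropout being excluded from the analysis.

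A reader might go on to infer that the trial is underpowered. The figures do not support that: the base calculation reproduces exactly, and the stated size holds 0.9 power up to about 9.2% dropout. This is a minor correction to a stated figure.

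**What to change.** Amend the padding sentence in the Power section. The simplest change keeps 120 per group and 360 in total, and states that this covers about 9.2% dropout, with power of about 0.898 if 10% of patients are lost to analysis. It costs one sentence and no additional patients.

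If the sponsor prefers to cover 10% in full with equal groups, the sentence should give 109/0.9 = 121.1, rounded up to 122 per group and 366 in total. That is 2 more per group and 6 more overall. Either way, printing the inflation formula would let a reader check the figure. The Study Design forecast needs no change on this account.
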